# Comparison of the efficacy between conventional moxibustion and smoke-free moxibustion on knee osteoarthritis: study protocol of a randomized controlled trial

**DOI:** 10.1186/s13063-017-1846-2

**Published:** 2017-04-24

**Keywords:** Moxa smoke, Moxibustion, Knee osteoarthritis, Randomized controlled trial, Protocol

## Abstract

**Background:**

Conventional moxibustion is a representative non-drug intervention in traditional Chinese medicine, and it has been reported to produce encouraging results and benefits in relieving symptoms and improving the quality of life for patients with knee osteoarthritis (KOA) in previous clinical trials and systematic reviews. Given that increasing concerns on the safety of generated smoke from conventional moxibustion have received much attention, smoke-free moxibustion is regarded as a potential alternative. However, whether smoke-free moxibustion would display a similar efficacy to that of conventional moxibustion still remains unclear. Therefore, this randomized controlled trial attempts to investigate the difference of efficacy between conventional moxibustion and smoke-free moxibustion in patients with KOA.

**Methods/design:**

This is a multicenter, randomized, single-blinded, parallel-group clinical trial. A total of 138 eligible participants with KOA will be randomly allocated to two groups (conventional moxibustion group and smoke-free moxibustion group) in seven hospitals in China. Participants will receive 12 sessions of moxibustion treatment at three acupoints (EX-LE4, ST35, and ST36) over a period of 4 weeks (3 sessions per week). A smoke-removing device is placed at the top of the moxibustion device for the smoke-free moxibustion group (*n* = 69), while the conventional moxibustion group (*n* = 69) is treated with traditional moxibustion. The primary outcome measure will be the change of the global scale of the Western Ontario and McMaster Universities Osteoarthritis Index (WOMAC) from the baseline to 4 weeks. Secondary outcomes include the visual analog scale VASand Patient Global Assessment scores. Follow-up measurements will be performed on the 8th and 12th weeks after random allocation.

**Discussion:**

This study will contribute to providing a solid foundation for the selection of moxibustion in clinical application as well as future research in moxibustion therapy.

**Trial registration:**

ClinicalTrials.gov, NCT02772055. Registered on 12 May 2016.

**Electronic supplementary material:**

The online version of this article (doi:10.1186/s13063-017-1846-2) contains supplementary material, which is available to authorized users.

## Background

Knee osteoarthritis (KOA) is the most common form of arthritis and is a major cause of disability and limitation of activity, especially in elderly patients [1]. It is characterized by pain and functional limitations, leading to a reduction in quality of life [2]. Osteoarthritis of the knee makes a significant impact on society, with more than 20 million Americans and 35 to 40 million Europeans developing this condition in their lifetime [3, 4]. Some recent international guidelines advocate non-pharmacological care for patients with knee pain [5–7]. As a representative non-drug intervention in traditional Chinese medicine (TCM) and a form of acupuncture [8–10], moxibustion has been reported to produce encouraging results and benefits in relieving symptoms and improving the quality of life for patients with KOA in many studies, including clinical trials and systematic reviews [11–15].

The mechanism of moxibustion is mainly related to its thermal effects, radiation effects, the pharmacological activity of moxa, and its combustion products (volatile oil, brown tar-like substances, and moxa smoke). Moxa smoke is a primary combustion product of moxibustion, and its potential effect on the health and environment may be controversial [16]. It was reported that moxa smoke has antibacterial and antiviral effects effective in treating various conditions including wound infections, vaginal itching, uterine prolapse, anal fistulas, common warts, and so forth [17–22]. However, some studies demonstrated that high levels of monoaromatic hydrocarbons, formaldehyde, and polycyclic aromatic hydrocarbons in the moxibustion room may have adverse effects on human health [23–25]. Epidemiological investigation also showed that the moxa smoke induced a variety of undesirable reactions such as dry throat, dry eye, and coughing [26]. Furthermore, with their increased environmental awareness, people have started to question the safety of the smoke produced by burning moxa [27–29]. Because of concerns as to the potential toxicity of the smoke, many acupuncturists prefer to use a smoke purification device to remove moxa smoke during the moxibustion treatment, but few studies have reported the difference of clinical efficacy between conventional moxibustion and smoke-free moxibustion (moxibustion using the smoke-removing device).

Thus, we are currently conducting a randomized controlled clinical trial to compare the efficacy of conventional moxibustion and smoke-free moxibustion for patients with KOA.

## Methods/design

### Design

This is a multicenter, randomized, single-blinded, parallel-group design clinical trial conforming to Consolidated Standards of Reporting Trials (CONSORT) and Standards for Reporting Interventions in Clinical Trials of Acupuncture (STRICTA) guidelines [30, 31]. A Standard Protocol Items: Recommendations for Interventional Trials (SPIRIT) checklist is provided in Additional file 1. A total of 138 eligible participants with KOA will be randomly allocated into two groups (moxibustion group or smoke-free moxibustion group) with a 1:1 allocation ratio. Eligible participants who meet the clinical criteria for KOA formulated by the American College of Rheumatology (ACR) will be enrolled in this trial [32]. Seven clinical research centers in China will participate in this trial: Central Hospital of ZiBo, Chengdu First People’s Hospital, Sichuan Second Hospital of TCM, Pi County People’s Hospital, Xinjin County TCM Hospital, Qionglai TCM Hospital, and Nanjing Hospital of TCM. The study period is 13 weeks, with a 1-week baseline period, 4-week treatment phase, and 8-week follow-up phase. After randomization, eligible participants will receive 12 sessions of moxibustion treatment over a period of 4 weeks. Patients will be assessed at the baseline visit, as well as at 2 weeks, 4 weeks, 8 weeks, and 12 weeks after allocation. The trial diagram demonstrates the procedures of the study (see Fig. 1). Table 1 outlines the measures used throughout this trial.

**Fig. 1 Fig1:**
[figure not shown]
Flowchart of the study process. Participants with a diagnosis of KOA will be recruited from seven centers. All project general practitioners (*GPs*) were trained for 1 day. The trial period will consist of 12 sessions of moxibustion treatment over a period of 4 weeks. The treatment frequency will be three sessions per week, and there will be a 2-month follow-up period. The outcomes will be measured at every visit

**Table 1 Tab1:** Study design schedule

Period	Inclusion	Treatment		Follow-up	
	Baseline	First assessment	Second assessment	Third assessment	Fourth assessment
	0 week	2 weeks after inclusion	4 weeks after inclusion	8 weeks after inclusion	12 weeks after inclusion
Inclusion confirmed	√				
Informed consent	√				
Randomization and blinding	√				
Sociodemographic characteristics	√				
Disease history	√		√		
Treatment history	√		√		
Comorbidity	√		√	√	√
Current treatment	√		√	√	√
Outcomes					
WOMAC	√	√	√	√	√
VAS	√	√	√	√	√
PGA		√	√	√	√
Trial evaluation					
Outcome analysis					√
Adverse event			√		
Causes of dropout			√		
Safety analysis			√		
Compliance analysis			√		

*WOMAC* Western Ontario and McMaster Universities Osteoarthritis Index, *VAS* visual analog scale, *PGA* Patient Global Assessment

### Inclusion criteria

Participants meeting the following criteria will be included: Aged between 40 and 75 years Diagnosed with KOA formulated by the American College of Rheumatology (ACR) Average severity of knee pain no more than 7 points on a visual analog scale (VAS) for most days during the past month Agreed to not use paregoric during the whole treatment phase Willingness to participate in a randomized study and to sign the informed consent form.

### Exclusion criteria

Participants will be excluded if they have any of the following conditions: Pain in the knee that may be caused by inflammatory, malignant, or autoimmune disease or by traumatic injury Serious diseases including cancer, uncontrolled hypertension, diabetes mellitus requiring insulin injection, life-threatening cardiovascular or neurological events, chronic respiratory disease, a hemorrhagic disorder, or serious mental diseases Knee replacement surgery, arthroscopy of the affected knee within the past year, steroid or hyaluronic acid injection in the knee joints within the previous 3 months Life-threatening cardiovascular or neurological events within the past year Physiotherapy or other treatments for osteoarthritis knee pain (with the exception of non-steroidal anti-inflammatory drugs) during the previous 4 weeks Current participation in another clinical trial Accepted acupuncture, moxibustion, cupping, or herbal medicine within the past 4 weeks.

### Sample size calculation

A power analysis has been undertaken before conducting this trial for further calculation. The significance level is 0.05, and the statistical power is 0.90, consistent with a previous trial on moxibustion for KOA and our pilot study [33]. To compensate for an anticipated dropout rate of 15%, 138 patients with KOA (69 in each group) will be recruited from seven centers in China.

### Recruitment strategies

There will be three strategies for KOA participant recruitment. First, participants will be recruited from the outpatient and inpatient departments of the seven hospitals. Second, printed recruitment posters will be distributed to local communities. Finally, advertisements will be posted in local newspapers and through the website.

### Random assignment

Each eligible subject will be randomly assigned to either the conventional moxibustion group or the smoke-free moxibustion group. A random number list will be generated with SPSS 16.0 (SPSS Inc., Chicago, IL, USA) by a statistician who is not directly involved with the study. The researchers in each clinical research center will call the independent statistician at the center for the randomized number, and the statistician will be immediately informed of the participant’s randomized number and treatment group by mobile message. The independent researcher will record the patient’s details and the number assigned to that patient. Central randomization has strict limits of authority: no one can check the files except the top principal investigator.

### Blinding

This is a single-blinded trial; participants are unaware of the assignments. Participants will be separated and treated in two different rooms. Meanwhile, the assessors of therapeutic effect, the data manager, and the statistician will be kept blinded to the treatment allocation. To prevent accidental un-blinding, there will be no contact between the study team and the subjects until after the data cleaning, database lockdown, and analysis are complete.

### Interventions

The treatment will be applied in 12 sessions, three times per week for 4 weeks. The conventional moxibustion group and the smoke-free moxibustion group will receive moxibustion at three standard acupuncture points: Neixiyan (EX-LE4), Dubi (ST35), and Zusanli (ST36) [11, 33] (Fig. 2). The selection of acupoints is based on TCM meridian theory to treat knee joint pain, known as the “Bi syndrome,” and on some similar studies [11, 12, 34–36]. All project general practitioners (GPs) have completed at least 5 years of training in acupuncture and moxibustion and are registered as Chinese medicine practitioners by the National Health and Family Planning Commission of the People’s Republic of China. Project GPs were trained for 1 day by an investigator who is an experienced medical acupuncturist, to standardize all aspects of the treatment protocol. To ensure implementation of the study, the investigator must maintain regular contact with the GPs to answer and settle any treatment-related problems. Each GP was provided with a detailed treatment manual describing administration of the moxibustion interventions as well as the trial protocol. Two separated moxibustion rooms were provided for the different groups by the centers, doors and windows will be opened in the treatment process. The participants are usually required to wear loose clothing to expose the knee joints and to maintain a comfortable sitting position for treatment.

**Fig. 2 Fig2:**
[figure not shown]
Acupoints used in the trial. The lines refer to the acupoints Dubi (ST35) and Zusanli (ST36) on the lateral side of the knee and Neixiyan (EX-LE4) on the medial side of the knee

### Moxibustion group (group A)

The moxibustion group will use a moxa device (Yijiu moxa device, Maanshan, Anhui, China) at the acupoints (EX-LE4, ST35, ST36). The moxa pillar is cylindrical, 1.5 cm in diameter, and 3 cm long. A lighted moxa pillar will be put into the moxa device attached at each acupoint, and the therapist will make sure the patient feels a warm but not scorching sensation (Fig. 3). One acupoint is treated for 30 min each time. Three acupoints are treated by moxibustion at the same time.

**Fig. 3 Fig3:**
[figure not shown]
Diagram of the moxibustion and smoke-free moxibustion devices. **a** This new moxa device is composed of three parts. **b** Participants are treated at acupoints Dubi (ST35), Zusanli (ST36), and Neixiyan (EX-LE4) with devices consisting of a moxa pillar. The moxa device has an opening in the center that allows heat and smoke from the burning pillar to stimulate the acupoints. **c** In the smoke-free moxibustion group, investigators place a purification device at the top of the moxibustion device to remove the moxa smoke

### Smoke-free moxibustion group (group B)

In contrast to the moxibustion group, a specifically designed device (Shenzhen Conyson Electronic Technology Co, Ltd., C200 moxa smoke purification device, Shenzhen, China) is applied to remove the moxa smoke for the smoke-free group in the process of moxibustion. Otherwise, the selection of acupoints and other interventions in both groups must be the same (Fig. 3).

### Outcome assessments

#### Primary outcome measurement

The primary outcome measure will be the mean change in the global scale value of the Western Ontario and McMaster Universities Osteoarthritis Index (WOMAC) from baseline to 4 weeks [37]. The WOMAC, one of the most widely used arthritis assessment tools, is composed of 24 questions to assess disability related to osteoarthritis. It includes three subscales to measure pain (5 questions), stiffness (2 questions), and physical function (17 questions) regarding KOA; higher scores indicate more severe impairment. All 24 questions will be listed in a numerical rating scale ranging from 0 (no symptoms) to 3 (maximum symptoms). If both knees are affected, the more severe knee will be assessed. Physicians who are blinded to the treatment allocation will help patients perform the self-assessment and collect and record the total score.

#### Secondary outcome measurements

The secondary outcomes include the mean changes in the VAS and Patient Global Assessment (PGA) scores. The pain intensity of KOA will be assessed using a 100 mm VAS (0, absence of pain; 100, the worst pain imaginable). The pain VAS is a standard tool in chronic pain studies for measuring pain intensity. We will evaluate the mean change in the VAS at baseline (0 week) and at 2, 4, 8, and 12 weeks after allocation. The PGA score is a self-reported 5-point measurement used to evaluate overall improvement after treatment. It has been used in various studies to assess therapeutic effects [38–40]. Participants individually evaluate their improvement by selecting one of 5 options (much improved, minimally improved, no change, minimally worse, or much worse) at 2, 4, 8, and 12 weeks from the baseline.

### KOA diary

Subjects will be provided with KOA diaries to record the specific time of knee pain attacks, the associated phenomena, and any medication used. This information will be recorded every day throughout the study period. All patients will be carefully instructed on how to use this diary to rate their symptoms.

### Statistical analysis plan

#### Data integrity

The research will ensure that no record will be missed or omitted in the original data source. Any corrections should be explained in the appended notes signed and dated by the physicians participating in the clinical trial. The primary input of the data is not permitted to be changed. After the observation of a clinical case, a case report form (CRF) will be submitted to the project directors for verification. The principal investigators will have full access to the data. The data manager will clarify any questions regarding the CRF with the researchers via clinical supervisors. Researchers should answer any questions as soon as possible so that the data manager will be able to conduct modification, validation, and input of the data. The data monitoring committee comprises a medical statistician and an epidemiologist, who are independent from the investigators and sponsors, for source data organizing, coding, and range checking for data values to ensure data quality.

### Analysis

The primary analysis of the data will be undertaken using the intention-to-treat principle with all randomized patients included in the analyses. A multiple imputation adjustment approach will be used for the missing data. Demographic and baseline data will be analyzed with standard, descriptive statistics. Between-group differences will be tested using repeated measure analyses of variance. The accepted level of significance for all analyses is *P* < 0.05. The whole data analysis process will be performed by statisticians who are independent from the research team and blinded to the group settings. SPSS software (SPSS 16.0, SPSS Inc., Chicago, IL, USA) will be used for the data analysis.

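### The repeated-measures ANOVA named for group comparisons is not tied to the primary endpoint, the week-4 WOMAC change, and its usual five-visit tests answer other questions

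*Protocol article*

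**What the plan says.** In the protocol article, Primary outcome measurement defines the endpoint as the "mean change in the global scale value of the Western Ontario and McMaster Universities Osteoarthritis Index (WOMAC) from baseline to 4 weeks". The Abstract gives the same endpoint.

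The Design section sets five assessment times: "Patients will be assessed at the baseline visit, as well as at 2 weeks, 4 weeks, 8 weeks, and 12 weeks after allocation". Table 1 lists WOMAC at all five. Treatment lasts 4 weeks, so weeks 8 and 12 are follow-up after treatment has ended.

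The Analysis section gives one comparative method for every outcome: "Between-group differences will be tested using repeated measure analyses of variance". It adds intention to treat, multiple imputation and a common 5% level ("The accepted level of significance for all analyses is" P < 0.05). It does not name the visits, the deciding model term, a planned contrast or any covariate.

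Sample size calculation gives "The significance level is 0.05, and the statistical power is 0.90" and 69 per group after allowing for 15% dropout. It states no difference or SD.

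**The concern.** A primary endpoint at one time point needs a test of that time point. A five-visit repeated-measures ANOVA offers two tests by default:

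- **Group main effect.** This averages the group difference over all visits. One is baseline, where randomisation makes the expected difference zero. Two come after treatment has stopped.
- **Group-by-time interaction, 4 df.** This asks whether the two profiles differ in shape anywhere.

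Neither is the week-4 change, and neither gives an estimate of it with a confidence interval. Two things are at stake. The P value reported as primary may answer a different question from the declared endpoint, in either direction. And with two F tests both at 5% and nothing saying which decides, the choice stays open until the results are seen.

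**Working it through.** **The plan's own figure.** The 138 cannot be reproduced, because no difference or SD is given. Working backwards, 58/0.85 = 68.2, which rounds up to 69 per arm. At two-sided 5% and 90% power, 58 per arm corresponds to (1.960 + 1.282) × √(2/58) = 0.602 SD. The figure is plausible for a two-group comparison with an effect of about 0.6 SD.

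**Inputs.** From the article: five visits, 69 per arm, 15% dropout (69 × 0.85 = 58.65, so 58 per arm), alpha 0.05. Assumed: two-sided testing, SD 1 at each visit, equal correlation r between visits, and the effect at each visit in SD units. The article supplies none of these assumed values.

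**Formulas** (n = 58, √(2/n) = 0.1857, r = 0.5)

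- Week-4 change: SD = √(2(1−r)) = 1.000. Noncentrality 0.6/0.1857 = 3.23, 114 df, **power 89%**.
- Week-4 ANCOVA on baseline: SD = √(1−r²) = 0.866. Noncentrality 0.6/(0.866 × 0.1857) = 3.73, 113 df, **power 96%**.
- Group main effect: SD of the five-visit mean = √((1+4r)/5) = 0.775. Noncentrality = mean effect/(0.775 × 0.1857), 114 df.
- Interaction: λ = (n/2) × Σ(effect − mean effect)²/(1−r), with 4 and 456 df.

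**Results at r = 0.5**

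| Effect at weeks 0, 2, 4, 8, 12 (SD) | Mean effect | Main effect: noncentrality, rejection rate | Interaction: λ, rejection rate | Week-4 change |
|---|---|---|---|---|
| 0, 0.3, 0.6, 0.3, 0.1 (wanes) | 0.26 | 1.81, 43% | 29 × 0.212/0.5 = 12.3, 81% | 89% |
| 0, 0.3, 0.6, 0.6, 0.6 (half effect at week 2) | 0.42 | 2.92, 83% | 29 × 0.288/0.5 = 16.7, 92% | 89% |
| 0, 0.6, 0.6, 0.6, 0.6 (sustained) | 0.48 | 3.34, 91% | 29 × 0.288/0.5 = 16.7, 92% | 89% |
| 0, 0, 0, 0.6, 0.6 (none at week 4) | 0.24 | 1.67, 38% | 29 × 0.432/0.5 = 25.1, 99% | 5% |

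The last row matters most. The declared endpoint shows no difference, yet the interaction is significant almost always.

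**Varying the correlation.** For the waning shape with r from 0.4 to 0.7, the main effect has 36–49% power and week-4 ANCOVA 94–99%. For the sustained shape at r = 0.3, the main effect has 97%, against 77% for the change score and 92% for ANCOVA.

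**Second calibration.** Here n = 59 per arm, and the week-4 effect is set at each r so that the change test has exactly 90% power.

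| Effect relative to week 4 (weeks 2, 4, 8, 12) | Main effect, r = 0.3 / 0.5 / 0.7 | Interaction |
|---|---|---|
| 1, 1, 1, 1 | 99.6 / 91.7 / 63.5% | 92.8% |
| 0.5, 1, 0.75, 0.5 | 88.9 / 63.4 / 35.4% | 78.8% |
| 0.5, 1, 0.5, 0 | 63.8 / 38.7 / 21.0% | 88.7% |

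The main effect therefore ranges from 21% to 99.6%, against 90% for the declared endpoint. ANCOVA gives 98.0 / 96.3 / 94.0%.

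**A version that does match.** If only weeks 0 and 4 are entered, λ = 29 × (0.3² + 0.3²)/0.5 = 10.44 = 3.23². The interaction is then identical to the t-test on change.

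**Centre.** At 59 per arm and 0.6 SD, unadjusted power is 90.3%. If centre explains 1%, 5% or 10% of the variance, adjusting for it gives 90.6%, 91.7% or 93.0%.

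**The case against.** The strongest reply is that one sentence in a condensed article does not fix the analysis to omnibus F tests on five visits. A two-visit model, or a planned week-4 contrast inside the five-visit model, would test the endpoint exactly. That stands. A reader might infer that the named method cannot test the primary endpoint, and the text does not support this. It supports only that the method is not linked to the endpoint.

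A reader might also infer that the plan ignores baseline and centre. The Analysis section neither includes nor excludes covariates, a full analysis plan may do so, and Random assignment describes no stratification by centre that would oblige adjustment. Baseline WOMAC is one of the repeated measurements and may enter that way. An unadjusted comparison of change is valid under randomisation, so baseline adjustment is a gain in precision and does not correct an error.

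Finally, a reader might infer that the test is bound to be diluted. That depends on an effect shape and correlation that the article does not give. With a sustained effect and r of 0.5 or less, the main effect has more power than the week-4 change test.

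The Analysis section also has independent, blinded statisticians carry out the analysis. This limits a choice between F tests made after seeing the data, but does not remove it, because no rule says which test decides.

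The mismatch itself survives. The article has its own section headed as the statistical analysis plan, fixes a single-visit endpoint and names a method whose usual outputs are not that contrast.

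**Conclusion.** The point holds as a gap between endpoint and test. The article declares a week-4 contrast and names a family of tests without saying which member tests it. With five visits entered, the default tests can miss a week-4 effect (main effect 43% against 89% in the waning case) or be significant without one (interaction 99% against 5%). They can also do as well or better (main effect 91% against 89% in the sustained case). Loss of power is possible but not established. What is established is that the primary conclusion could rest on a question other than the declared one.

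These figures assume 58 per arm, equal correlation between visits, equal SDs and the effect shapes shown. The mismatch depends on none of them. Centre adjustment is optional, with a gain of about 0.3 to 3 percentage points under the assumed centre shares.

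**What to change.** In the Analysis section or the full analysis plan, before database lock and unblinding:

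1. State that the primary test is the between-group difference in WOMAC total at week 4, with its 95% CI, adjusted for baseline WOMAC. Use ANCOVA, or a mixed model for repeated measures with treatment-by-visit terms. With baseline in the model, the treatment effect on the week-4 score and on the change to week 4 is the same, so the declared endpoint is kept.
2. Pool this estimate and its standard error over the planned imputations by Rubin's rules.
3. Make the week 2, 8 and 12 differences secondary.
4. State that the omnibus group and group-by-time F tests are not used for the primary conclusion.
5. Optionally add centre as a covariate, at a cost of six degrees of freedom for seven hospitals.

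The cost is one paragraph of wording and no new data. At r = 0.5, 58 per arm and 0.6 SD, baseline adjustment raises power from about 89% to 96%.
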